**Methods:**

Eligible participants are adults who seek health care for musculoskeletal pain and who are at risk of developing persistent pain, physical disability, and sickness absence. Participants may be recruited from primary care rehabilitation centres or primary care healthcare centres in Region Västra Götaland. Participants will be randomised to treatment according to the PREVSAM model (intervention group) or treatment as usual (control group). The PREVSAM model comprises an interdisciplinary, person-centred rehabilitation programme, including coordinated measures within primary health care, and may include collaboration with participants’ employers. The primary outcome sickness absence is operationalised as the number and proportion of individuals who remain in full- or part-time work, the number of gross and net days of sickness absence during the intervention and follow-up period, and time to first sickness absence spell. Secondary outcomes are patient-reported short-term sickness absence, work ability, pain, self-efficacy, health-related quality of life, risk for sickness absence, anxiety and depression symptoms and physical disability at 1 and 3 months after inclusion (short-term follow-up), and at 6 and 12 months (long-term follow-up). A cost-effectiveness analysis is planned and drug consumption will be investigated.

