### Outcomes

#### Primary outcome

##### Sickness absence

Sickness absence will be measured using the proposed outcome measures from the Swedish Social insurance report 2016:9 [31]. These measures are based on sick-leave data at the individual level (including diagnoses) of all sick-leave spells longer than 14 days in which sickness cash benefits were provided by the SSIA. Data will be retrieved from the MiDAS database (preventive sickness absence will be excluded as this might be part of intervention). All sickness absence is planned to be analysed, but the main focus is on sickness absence relevant to musculoskeletal pain. Sickness absence was chosen as primary outcome because it is a frequent consequence of musculoskeletal pain, and it is of relevance for both the individual, the employer and society to measure and target this outcome when testing and implementing a new rehabilitation model for this patient group.

Sickness absence will be operationalised as:
Number and proportion of individuals who were on sickness absence and/or the number and proportion of individuals who remain in full- or part-time work during the follow-up period.Number of gross and net sick-days during the follow-up period.Time to first sickness absence spell.

Short-term sickness absence (≤ 14 days) is not reported to the SSIA among employed participants. They have sick pay from their employer the first 2 weeks of a sick-leave spell. Thus, short-term sickness absence will be measured using self-reported responses to weekly text messages via mobile phone (SMS-Track ApS, Denmark, www.sms-track.com). The participants will enter a number from 0 to 7 in response to the question “Have you been absent from work during the past week due to your musculoskeletal pain, and if so for how many days?”. However, unemployed participants have sickness benefits from the SSIA from the second day of a sick-leave spell.

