### Statistical analyses

Primary outcomes are sickness absence and sick days, where the first outcome is binary and the second one is continuous and most likely skewed [47]. Sick leave regardless of reason will be retrieved. However, sick leave for diseases of the musculoskeletal system and connective tissue is of specific interest. Sample size calculations will be based on the general assumptions that we want a power of 80% and that statistical significance is set to α = 0.05. For the outcome sickness absence, the difference between the proportion of sickness absence = yes/no will be compared between the intervention (PREVSAM model) and control (TAU) group. We assume that approximately 30% in the control group will have sickness absence = yes at least one time during the 12 month follow-up period [48]. If the percentage of sickness absence = yes in the intervention group is assumed to be 15% or 20%, then the sample size in each group needs to be 312 individuals and 132 individuals, respectively. To detect a difference of 15% (30% with sickness absence in control group and 15% with sickness absence in intervention group), a total sample size of 264 (132 individuals in each group) would give approximately 80 cases to analyse for the primary outcome sick days. This would enable us to estimate 8 parameters in a logistic regression analysis. This would mean a power of about 75% to detect a difference of at least 0.6 Ln (sick days), if the standard deviation for Ln (sick days) is assumed to be 1. This is equal to a scenario with mean sick days of about 35 in the intervention group (PREVSAM model) and 68 in the control group (TAU). This would enable us to perform linear regression analysis adjusting for several covariates and estimating about 7 parameters. To summarise these calculations and allowing for dropouts, randomisation of 200 individuals to each group is required. An interim analysis will be performed for the primary outcome when 50% of patients have been randomised and have completed the 12 months follow-up. At the same time-point it might be possible to perform the short-term follow-up analyses. The interim analysis will be performed by a statistician, blinded to the treatment allocation. The statistician will report and discuss the results of the interim analysis with the steering committee in a joint meeting. The steering committee decides on the continuation of the trial.

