Group characteristics will be presented as mean and standard deviations, median and 25th and 75th percentile or the number and percentage. For the primary outcomes descriptive analyses for sickness absence for the two groups will be presented according to recommendations [31]. The sickness absence will be presented with number of individuals who had sickness absence during the follow-up period. Proportions of individuals with sickness absence per month will be presented. The number of sick days (gross and net) with sickness benefit during the follow-up periods will be presented with mean and median values. For participation in work life additional measures will be presented with descriptive statistics regarding time to sick-leave spell for musculoskeletal pain. Number of days before a sick leave spell > 14 days occurs and number and duration of sick-leave spells per individual will be presented for gross and net days. Outcomes will be analysed according to intention-to-treat. Multivariable logistic regression analysis will be used for the primary outcome sickness absence during the follow-up period [1], not being sickness absent (0) adjusted for confounders. Multivariable linear regression analyses, or possibly quantile regression, will be used to evaluate differences between groups for sick leave days, among those have at least one sick leave spell. All other measurements will be analysed by calculating raw differences between baseline and follow-up assessments. Parametric and non-parametric tests will be used depending on data level and distribution. Sub-group analyses can be performed in regard to characteristics of interest, such as diagnosis or sick-leave. The level of significance is set to *p* < 0.05. Relevant statistical programs will be used for the statistical analyses, for example the IBM SPSS, SAS, STATA.

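### Time to first sickness absence spell is listed under the primary outcome, but the statistics section only describes it, with no group comparison or censoring

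*Protocol article*

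**What the plan says.** Time to first spell has a different status in different parts of the protocol article.

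- The abstract (Methods) counts it in the operationalisation of the primary outcome: "and time to first sickness absence spell".
- Under Primary outcome, Sickness absence, it is the third of three operationalisations: "Time to first sickness absence spell".
- Statistical analyses, first paragraph, names two primary outcomes and leaves it out: "Primary outcomes are sickness absence and sick days, where the first outcome is binary and the second one is continuous and most likely skewed".
- Statistical analyses, second paragraph, treats it as supplementary and limits it to musculoskeletal pain: "additional measures will be presented with descriptive statistics regarding time to sick-leave spell for musculoskeletal pain". Its form is given next: "Number of days before a sick leave spell > 14 days occurs and number and duration of sick-leave spells per individual will be presented".

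The same paragraph assigns multivariable logistic regression to absence yes/no. It assigns linear or possibly quantile regression to sick days, restricted to people with at least one spell. Remaining measurements get raw differences between baseline and follow-up. Outcomes are to be analysed by intention-to-treat.

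**The concern.** There are two problems. First, a measure cannot be both a component of the primary outcome and an additional descriptive item. A reader of the results could not tell which status was intended.

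Second, the analysis given does not suit a time-to-event measure. No group comparison, censoring rule or survival method is stated. The general rule of baseline-to-follow-up differences cannot fill the gap, because time to a first spell has no baseline value. A count of days before a spell exists only for people who have one. If the summary covers those people alone, it compares groups selected by a post-randomisation event, and similar averages in the two arms could be misread as showing that the programme does not delay sick leave.

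**Working it through.** **Inputs (Statistical analyses).** Control: "approximately 30% in the control group will have sickness absence = yes at least one time during the 12 month follow-up period". Design contrast: "30% with sickness absence in control group and 15% with sickness absence in intervention group". Power 80%, alpha 0.05 (two-sided assumed; the sidedness is not stated), 132 per group before dropout, 200 per group randomised.

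**The plan's own figure.** For 30% vs 15%, the pooled two-proportion formula gives 121 per group without and 134 with continuity correction. The plan states 132, so its figure is reproduced to within two patients. (The sentence pairing 312 and 132 with 15% and 20% has them in reversed order; the sentence after it confirms that 132 belongs to 15%.)

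**People without a spell.** 1 − 0.30 = 70% in control and 1 − 0.15 = 85% in intervention.

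**Added assumption.** The hazard is constant over 12 months. Per year, h = −ln(0.70) = 0.357 in control and −ln(0.85) = 0.163 in intervention. The hazard ratio is 0.1625/0.3567 = 0.456.

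**Formulas**, with p the 12-month risk and results multiplied by 365:

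- Mean among cases: 1/h − (1 − p)/p. Control: 2.804 − 2.333 = 0.470. Intervention: 6.153 − 5.667 = 0.486.
- Median among cases: −ln(1 − p/2)/h. Control: 0.1625/0.3567 = 0.456. Intervention: 0.0780/0.1625 = 0.480.
- Mean spell-free time within 12 months, all participants: p/h. Control: 0.30/0.3567 = 0.841. Intervention: 0.15/0.1625 = 0.923.

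| Summary (days) | Control | Intervention | Gap |
|---|---|---|---|
| Mean, cases only | 172 | 178 | 6 |
| Median, cases only | 166 | 175 | 9 |
| Quartiles, cases only | 80 to 261 | 86 to 268 | 6 to 7 |
| Spell-free time, all participants | 307 | 337 | 30 |

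With the plan's other scenario, 20% in the intervention group, the cases-only mean there is 176 and the median 172. Spell-free time is 327 days, a gap of 20.

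**Dependence on the constant hazard.** The pattern needs only proportional hazards. Half of the control cases have occurred when control survival is 0.85. Intervention survival is then 0.85^0.456 = 0.929, so (1 − 0.929)/0.15 = 47.6% of intervention cases have occurred. The two timing distributions nearly coincide.

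**Rank test among cases.** In 3,000 simulated trials per sample size under these hazards, it rejected in 5.3% (132 per group) and 5.7% (200 per group), about the nominal 5%.

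**Power of comparisons that use everyone.** Expected events: 132 × (0.30 + 0.15) = 59, and 200 × 0.45 = 90. Log-rank power by Schoenfeld's formula is Φ(√d/2 × |ln 0.456| − 1.96).

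| Test | 132 per group | 200 per group |
|---|---|---|
| Yes/no, two proportions | 83.5% | 95% |
| Log-rank, Schoenfeld | 86% | 96% |
| Yes/no, simulated chi-square | 84.4% | 95.6% |
| Log-rank, simulated | 84.5% | 95.4% |

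**The case against.** The strongest reply is that nothing says people without a spell are dropped from the time summary. The restriction to people with a spell is written only for the sick-days regression. Descriptive statistics can include a Kaplan-Meier curve, the descriptive analyses are said to follow a cited recommendation that is not at hand, and an unseen analysis plan may handle censoring. This stands in part: the cases-only reading is an inference. It remains the natural one, because "Number of days before a sick leave spell > 14 days occurs" has no value for someone who never has a spell.

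It can also be said that the statistics section may legitimately treat the measure as supportive. That is so, but then the abstract and the outcome section should not list it under the primary outcome.

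A reader might go further and infer that the trial would miss a halved risk. The documents do not support that. Absence yes/no is compared in all participants by logistic regression, the sample size rests on that contrast, and month-by-month proportions absent are also to be shown. Nor does the lack of a survival analysis cost meaningful power: by formula the log-rank test gains about 1 to 2 percentage points, and in simulation the two tests are practically equal.

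**Conclusion.** The conflict over the measure's status stands on the text alone and needs no assumption. So does the absence of any stated group comparison or censoring.

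The numerical consequence is conditional. If days are summarised only among cases, that summary says almost nothing about delay: a 6-day gap in means and a 9-day gap in medians, where spell-free time in all participants differs by 30 days. This rests on the plan's assumed rates of 30% and 15% and on constant hazards, although the near-coincidence of timing among cases needs only proportional hazards. The assumed rates are stated for sickness absence in general. The time measure is narrowed to musculoskeletal spells over 14 days, whose rate is not given, so the share without a spell could exceed 70% and 85%.

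The harm is confined to this one measure, and the main binary comparison is unaffected. It is worth correcting before analysis but does not threaten the trial.

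**What to change.** Reconcile the abstract and the Sickness absence section with the Statistical analyses section in one of two ways.

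1. Keep an analysis of the measure. Define it as time from randomisation to first spell over 14 days in all randomised participants, censored at 12 months or at the end of register access. Show Kaplan-Meier curves, with a Cox model or a difference in 12-month restricted mean time. Label it as supportive to the binary outcome, so that no further primary test is added.
2. Stop listing it under the primary outcome, and describe it with Kaplan-Meier curves in all participants.

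Either way, state whether it covers all spells or musculoskeletal spells only, and do not use days to spell among cases as evidence of effect. With 70% and 85% expected to be spell-free, the Kaplan-Meier median would not be reached in either group, so report the curve or the restricted mean instead.

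The cost is a few lines of wording. Individual-level register data on spells over 14 days are already to be retrieved, and presenting days before a spell already requires their dates.

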### Aims

The aim of the study is to evaluate effects of an early intervention, the PREVSAM model, on the prevention of sickness absence and development of persistent pain in at-risk patients with musculoskeletal pain. The study will also evaluate effects of the PREVSAM model on patient-reported work ability, risk for sickness absence, musculoskeletal pain status, self-efficacy, health-related quality of life, physical disability, depression and anxiety symptoms, and drug consumption. Cost-effectiveness of the model will be evaluated.

Research questions:

Q1: Is the PREVSAM model more effective in preventing sickness absence, compared with treatment as usual, in patients with musculoskeletal pain who have been identified to be at risk for sickness absence?

Q2: Do patients participating in the PREVSAM model report higher work ability, improved pain status, better self-efficacy, less physical disability or higher health-related quality of life, compared with those who receive treatment as usual at follow-up?

Q3: Is there a patient-reported reduced risk (using the ÖMPSQ score) for sickness absence in patients participating in the PREVSAM model, compared with those who received treatment as usual at follow-up?

Q4: Can any effects be seen in regard to anxiety and depression symptoms or drug consumption in patients participating in the PREVSAM model, compared with those who receive treatment as usual?

Q5: Is the PREVSAM model more cost-effective compared with treatment as usual?

The study hypothesis is that a person-centred rehabilitation, illuminating and emphasizing responsibilities, using interdisciplinary teamwork which can also include collaboration with the employer and/or workplace, in an early stage before symptoms are manifest and consequences in form of sickness absence have become established, will be more effective than treatment as usual in prevention of sickness absence.

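### Sick days, a primary outcome, are tested only among participants who had a spell; that is not a randomised comparison and can hide, reverse or exaggerate an effect.

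*Protocol article*

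**What the plan says.** All of this is in the Protocol article.

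- Statistical analyses opens with: "Primary outcomes are sickness absence and sick days, where the first outcome is binary and the second one is continuous and most likely skewed". Under Primary outcome, Sickness absence, gross and net days are counted over follow-up, with no limit to those who had a spell.
- Statistical analyses also states: "Outcomes will be analysed according to intention-to-treat".
- Shortly afterwards, linear or possibly quantile regression "will be used to evaluate differences between groups for sick leave days, among those have at least one sick leave spell".
- The hypothesis in Aims is that the programme "will be more effective than treatment as usual in prevention of sickness absence". The sample size uses "30% with sickness absence in control group and 15% with sickness absence in intervention group".
- Any absence is analysed by logistic regression without this restriction. Mean and median gross and net days are to be described. The section gives no between-group test of days in all randomised participants, and no model that joins the any-absence and days parts.

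**The concern.** The set of people analysed for sick days is defined by the other primary outcome. A participant with no registered days is not missing: zero is a valid value, and it is the result the programme aims for. If PREVSAM changes who has a spell, the PREVSAM cases and the TAU cases are differently selected groups, and randomisation no longer protects their comparison. Adjustment for baseline covariates does not reliably restore that protection.

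At stake is the reading of a primary outcome. A real fall in total sick days could appear as no difference, or as longer absence under PREVSAM. Equally, the analysis could credit PREVSAM with shortening spells that it left unchanged.

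**Working it through.** **Inputs from the Protocol article, Statistical analyses.** Any absence 30% v 15%; 132 per arm (264 in total) before dropout; about 80 cases for sick days; difference of 0.6 in Ln days; SD of Ln days 1; power about 75%; mean days 35 v 68; α = 0.05 (sidedness not stated, two-sided assumed).

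**The plan's own figure.** With 40 v 40 cases, the standardised difference is 0.6 / √(1/40 + 1/40) = 2.68, and Φ(2.68 - 1.96) = 0.765. The noncentral t gives 75.5%. The stated 75% is therefore reproduced, and it is a calculation on cases only. The 80 cases match 264 × 0.30 = 79.2, which is the count if PREVSAM has no effect on having a spell. The plan's own rates give 132 × 0.30 + 132 × 0.15 = 39.6 + 19.8 = about 59 cases. With 40 v 20, 0.6 / √(1/40 + 1/20) = 2.19 and Φ(2.19 - 1.96) = 0.59 (58% by noncentral t). So the power statement also treats the number of cases as unaffected by treatment.

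**Who is left out.** 1 - 0.30 = 70% of TAU and 1 - 0.15 = 85% of PREVSAM.

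**What the restricted contrast estimates.** Assumptions: Ln days among TAU cases are normal with SD 1 and mean 68 days, so the mean of Ln days is ln 68 - 0.5 = 3.72. PREVSAM prevents half of the spells that would have occurred and leaves the others unchanged. TAU days per randomised person are 0.30 × 68 = 20.4. Only the choice of which half is prevented varies.

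- *Shorter half prevented.* Difference in Ln days among cases: √(2/π) = +0.80. Mean days among PREVSAM cases: 68 × 2 × Φ(1) = 68 × 2 × 0.8413 = 114.4. Days per randomised person: 0.15 × 114.4 = 17.2, a fall of 16%.
- *Random half prevented.* Difference among cases: 0.00. Days per randomised person: 0.15 × 68 = 10.2, a fall of 50%.
- *Longer half prevented.* Difference among cases: -0.80. Mean days among PREVSAM cases: 68 × 2 × 0.1587 = 21.6. Days per randomised person: 0.15 × 21.6 = 3.2, a fall of 84%.

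Days per randomised person fall in all three cases and no remaining spell is altered. Yet the contrast among cases runs from a ratio of exp(-0.80) = 0.45 to exp(0.80) = 2.2.

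**How often a trial would show this.** Simulation with 132 per arm, t-test on Ln days among cases:

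- Shorter half prevented: significant against PREVSAM in about 92% of trials. A rank test in all randomised participants, zeros included, favours PREVSAM in about 70%.
- Random half prevented: the test among cases is significant in about 5%, both directions together. The all-randomised rank test favours PREVSAM in about 82%.
- The plan's own shortening (35 v 68, ln(35/68) = -0.66) with a random half prevented: significant in favour of PREVSAM in about 65%, and practically never against it.

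**The case against.** The strongest reply is that the plan does not ignore the zeros. Any absence is modelled by logistic regression without the restriction, days are modelled among cases, and the pair has the structure of a two-part analysis. Means and medians of days are also described, with no stated limit to cases. A reader would see the lower incidence beside the conditional result. This stands as mitigation. It does not supply a between-group test of days by randomised arm, because the two parts are never combined.

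It can also be said that participants stay in their allocated arm, so intention-to-treat is not breached in that sense. That is fair as far as allocation goes. The conflict lies in the analysis set, which leaves out randomised people because of their outcome.

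Two stronger readings are tempting and not supported:

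- *That the analysis will point against PREVSAM.* The document does not say which spells would be prevented. Preventing the longer ones moves the contrast in PREVSAM's favour, and the plan's own scenario gives the right direction. The 92% depends on the assumption that the shorter half is prevented. The log-normal model is also only approximate: Φ((ln 14 - 3.72)/1) = Φ(-1.08), so it puts about 14% of spells at or below 14 days, and the register does not hold such spells for employed participants.
- *That "Time to first sickness absence spell" has the same fault.* The plan describes "Number of days before a sick leave spell > 14 days occurs" among descriptive statistics. It does not say that people without a spell are dropped, and a descriptive presentation can allow for censoring. The detail can be left to a fuller plan.

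**Conclusion.** The point holds for the inferential comparison of sick days. As written, it conditions on a post-randomisation outcome that treatment is expected to halve, so it is not a randomised comparison and does not fit the intention-to-treat principle stated in the same section.

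The possible distortion is large and its direction unknown: about -0.80 to +0.80 in Ln days among cases when half of the spells are prevented and the rest are unchanged. For comparison, the plan wants to detect 0.6. These limits rest on log-normal days with SD 1 and on the two extreme patterns of prevention. The middle case needs no selection by length, and there a halving of days per randomised person gives no expected difference in the stated regression. The any-absence analysis, which sets the 264, is not affected.

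**What to change.** Make the confirmatory comparison of sick days one in all randomised participants, with zero for those without a spell. Suitable choices are a rank-based or permutation test, or a two-part model combined to the marginal mean. Report the difference in mean days per randomised participant with a bootstrap interval as the estimate. Keep the regression among cases, labelled as conditional on having a spell and descriptive.

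This needs new analysis wording and modest programming, but no new data. There are two costs:

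- The power statement for sick days must be redone, since the present one applies to cases only.
- The test should not rest on mean days alone. At 132 per arm it has only about 8% power if the shorter half is prevented and about 45% if a random half is, against about 70% and 82% for the rank test. With most values at zero, however, the rank test mainly reflects who had a spell, so the estimate in days must stand beside it.
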